#### Changes in maternal body weight and body fat distribution comparing the intervention arm to control arm at 20 weeks

Separate multivariate linear regression models will be fit to analyze the effect of randomization group on body weight or body fat distribution (waist circumference) at the end of intervention at 20 weeks. Body weight or waist circumference at 20 weeks will be considered as the outcome, with independent covariates including baseline weight or waist circumference, randomization group and other potential confounders. The distributions of body weight and waist circumference will be examined graphically and appropriate transformations (e.g., natural logarithm) will be considered. The statistical significance of the effect of randomization group on outcome will be assessed through a likelihood ratio test.

#### Changes in FV consumption, maternal body weight and body fat distribution comparing the intervention arm to control arm at 1 year

As described above, separate multivariate linear regression models will be fit to analyze the effect of randomization group on (1) average number of servings of FV consumed, (2) body weight and (3) body fat distribution (waist circumference) at the end of intervention at year 1.

### Power and sample size calculations

Power calculations for linear mixed models with adjustment for multiple testing were carried out through simulation studies. Due to computational considerations, adjustment for multiple testing was carried out through a conservative Bonferroni correction procedure to maintain the overall type I error at 0.05. CpG measurements (1a): In each dataset, we simulated repeated measurements of CpG levels according to a multivariate normal distribution with unit variance, assuming a within-subject correlation ρ, a mean difference in levels in the *control group* comparing baseline to the 20-week (T2) visit equal to 0.1 SD units and a mean difference in the intervention group between the 20-week (T2) and baseline (T0) of Δ SD units. The threshold for statistical significance was set at p = 0.05/300000, corresponding to a Bonferroni correction to maintain the overall Type I error at 0.05. When the correlation between the repeated CpG measurements is set to ρ = 0.5 (ρ = 0.3), a sample size of 200 per group results in 99% (82%) power to detect a mean difference in the intervention arm between baseline and T2 of Δ = 0.75 SD units, obtained by averaging over 100 simulated datasets. For the analysis of the 12 inflammatory markers, we simulated repeated measurements of inflammatory marker levels according to a multivariate normal distribution as described above. Assuming a Bonferroni correction to maintain the overall Type I error at 0.05 and when the correlation between the repeated inflammatory measurements is set to ρ = 0.5 (ρ = 0.3), a sample size of 200 per group results in 94% (84%) power to detect a mean difference in the intervention arm between baseline and T2 of Δ = 0.45 SD units, obtained by averaging over 100 simulated datasets.

Power calculations for the analyses of body weight, waist circumference and fruit and vegetable consumption at 1 year were based on a generalized linear model, using the R package pwr [32]. A sample size of 400 subjects results in 98% power to detect an effect size of 0.05 or larger, assuming a two-sided test and a type I error 0.05. We assumed the same variability at the two time points so the power is the same for 20 weeks and one year.

Previous studies found a reduction of 3.90 kg in the intervention arm compared to the control group in weight change from baseline, with an associated SD of approximately 4.8 kg [33]. A 98% power to detect an effect size of 0.05 or larger would correspond to a difference in weight change of 0.24 kg or larger between the two randomized groups. Previous studies found a reduction of 7.4 cm in the diet-intervention arm compared to the control group in waist circumference change from baseline, with an associated SD of approximately 15 cm [34]. A 98% power to detect an effect size of 0.05 or larger would correspond to a difference in waist circumference change of 0.75 cm between the two randomized groups. Our preliminary data showed a mean increase in fruit/vegetable consumption in the diet intervention arm of 7.3 servings with an associated SD of approximately 3 servings [35]. A 98% power to detect an effect size of 0.05 or larger would correspond to a difference in fruit/vegetable consumption change of 0.15 servings between the two randomized groups.

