#### Changes in inflammatory markers and methylation profiles comparing the intervention arm to control arm

To conserve power for the DNA methylation analysis, we will analyze approximately the most variable 300 K DNA methylation profiles. Each inflammatory and methylation marker will be analyzed in separate linear mixed effects models with a random intercept to account for the within subject correlation of the repeated measurements obtained at baseline and 20 weeks. Prior to analysis, each marker will be natural logarithm transformed to satisfy normality assumptions. Each linear mixed effects model will be of the form: E(Y_ij_) = β_0_ + β_1_ x T_ij_ + β_2_ x G_i_ + β_3_ x G_i_ x T_ij_, where Y_ij_ denotes the CpG or inflammatory marker measurement for subject *i* at visit *j*, T_ij_ is the time (post randomization) for subject *i* at visit *j* and G_i_ denotes the randomization group for subject *i*. The primary hypothesis test of interest is H_0_: β_3_ = 0, testing the interaction of randomization group with time, using a likelihood ratio test. As a secondary analysis, we will also consider a linear model in which the baseline CpG level is included as an additional covariate. Missing data imputation methods will be considered to confirm the robustness of the findings. Adjustment for multiple comparisons will be based on the False Discovery Rate (FDR) procedure of Benjamini and Yekutiel [31], which allows for correlation between CpG or inflammatory marker levels. Threshold for statistical significance will be based on the raw p value that controls the rate of false discoveries to be under 5%. The adjustment for multiple testing will be carried out separately for the set of 300,000 CpG measurements and the set of 12 inflammatory markers.

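### Power is quoted under a Bonferroni rule called conservative, but the planned Benjamini-Yekutieli rule is stricter when few CpGs or markers respond, so the quoted power is not a lower bound

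*Protocol article*

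**What the plan says.** Two sections of the protocol article name different multiplicity rules for the same tests.

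- **Planned analysis** (Data analysis, section on changes in inflammatory markers and methylation profiles). Each CpG and each marker is analysed in its own mixed model, "testing the interaction of randomization group with time, using a likelihood ratio test". Then: "Adjustment for multiple comparisons will be based on the False Discovery Rate (FDR) procedure of Benjamini and Yekutiel". The false discovery rate is to be held under 5%, and the adjustment is made "separately for the set of 300,000 CpG measurements and the set of 12 inflammatory markers". The stated reason for this procedure is that it allows for correlation among the measurements.
- **Power** (Power and sample size calculations). For computational reasons, "adjustment for multiple testing was carried out through a conservative Bonferroni correction procedure to maintain the overall type I error at 0.05". For the CpGs, "The threshold for statistical significance was set at p = 0.05/300000". With 200 women per group and ρ = 0.5 (0.3), the stated power is 99% (82%) for CpGs at Δ = 0.75 SD and 94% (84%) for the 12 markers at Δ = 0.45 SD, from 100 simulated datasets.

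Neither section gives power under the planned procedure or says how many CpGs or markers are expected to respond.

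**The concern.** A power calculation may use a simpler rule than the analysis if the simpler rule is never the more lenient of the two. A reader told that a conservative correction stood in for a false discovery rate procedure will take the quoted power as a floor. That would be true if the analysis used Benjamini-Hochberg, which never rejects less than Bonferroni at the same level. It is not true of BY, which divides every step-up threshold by a further factor to protect against arbitrary dependence. Methylation and the inflammatory markers are primary outcomes, so if the diet changes only a few of them, the trial may be less able to show it than the figures suggest.

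**Working it through.** **Inputs.** From the power section: 200 per group, unit variance, ρ = 0.5 or 0.3, a control-arm change of 0.1 SD, an intervention-arm change Δ of 0.75 SD (CpGs) or 0.45 SD (markers), and an overall level of 0.05. From the data analysis section: families of m = 300,000 and m = 12, BY at 5%, and a likelihood ratio test of one interaction term, treated here as a two-sided test.

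**Step 1: reproduce the stated power under Bonferroni.** The SD of a change is √(2(1−ρ)), so the standard error of the between-arm difference in change is √(2(1−ρ)) × √(2/200). This is 0.100 at ρ = 0.5 and 0.118 at ρ = 0.3. Power ≈ Φ(net/SE − z), where z is the two-sided critical value at 0.05/m: 5.233 for CpGs and 2.865 for markers.

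| Family | Net difference | Bonferroni power, ρ = 0.5 (0.3) | Stated |
|---|---|---|---|
| CpG | 0.75 (Δ itself) | 98.8% (86.6%) | 99% (82%) |
| CpG | 0.65 (Δ − 0.1) | 89.7% (60.3%) | 99% (82%) |
| Marker | 0.45 (Δ itself) | 94.9% (82.6%) | 94% (84%) |
| Marker | 0.35 (Δ − 0.1) | 73.7% (53.7%) | 94% (84%) |

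The stated figures are approximately recovered only if Δ is the between-arm difference. The largest gap is 86.6% against 82%. A t-test version gives 84.1% there, and 100 datasets leave a standard error of √(0.82 × 0.18/100) = 3.8 points. The text as written implies the net values after subtraction, so both readings are carried forward.

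**Step 2: the BY cut-offs.** BY compares the k-th smallest p-value with k × 0.05/(m × c(m)), where c(m) = 1 + 1/2 + … + 1/m.

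- CpGs: c(300,000) = 13.19. The first-step cut-off is 0.05/(300,000 × 13.19) = 1.26e-8, against 0.05/300,000 = 1.67e-7.
- Markers: c(12) = 3.10. The first-step cut-off is 0.05/(12 × 3.10) = 0.00134, against 0.05/12 = 0.00417.

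The BY threshold exceeds Bonferroni's once k > c(m), that is from the 14th CpG or the 4th marker declared.

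**Step 3: one true signal.** The same formula with z at 0.05/(m × c(m)), which is 5.691 for CpGs and 3.207 for markers:

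| Family | Net difference | BY, ρ = 0.5 (0.3) | Bonferroni | Loss in points |
|---|---|---|---|---|
| CpG | 0.75 | 96.5% (74.1%) | 98.8% (86.6%) | 2.3 (12.5) |
| CpG | 0.65 | 79.1% (42.2%) | 89.7% (60.3%) | 10.6 (18.1) |
| Marker | 0.45 | 90.2% (72.5%) | 94.9% (82.6%) | 4.7 (10.1) |
| Marker | 0.35 | 61.5% (40.2%) | 73.7% (53.7%) | 12.2 (13.5) |

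**Step 4: more than one true signal.** Average power by simulation of the full step-up rule, with independent tests, ρ = 0.3 and net = Δ:

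| True CpGs | Bonferroni | BY | | True markers | Bonferroni | BY |
|---|---|---|---|---|---|---|
| 1 | 86.5% | 74.9% | | 1 | 82.8% | 73.8% |
| 10 | 86.5% | 84.6% | | 3 | 83.3% | 82.0% |
| 15 | 86.5% | 86.4% | | 4 | 82.0% | 82.8% |
| 20 | 86.6% | 87.8% | | 6 | 82.5% | 86.4% |
| 100 | 86.5% | 93.0% | | 12 | 82.4% | 91.3% |

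Across both values of ρ and both readings of Δ, the two rules cross at about 13 to 25 true CpGs and 3 to 6 true markers. A further simulation of the markers at ρ = 0.3, with a correlation of 0.4 between them, gave nearly the same picture: 73% (BY) against 83% (Bonferroni) for one true marker, and 83% for both rules with four.

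**The case against.** A reader might infer that the planned analysis simply has less power than stated. The documents do not support that. BY is a step-up rule and overtakes Bonferroni when enough signals are present. The article's hypothesis is broad, concerning methylation patterns and an inflammatory profile, and its background cites three blood markers that respond to such diets. With three true markers or ten true CpGs the loss in the last table is under 2 points, which is less than the simulation error of the stated power at ρ = 0.3. A material loss needs nearly isolated signals, and nothing in the article says that is the expected case. All of this stands.

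It can also be said that *conservative* merely describes Bonferroni's control of type I error and promises nothing about power. The wording allows that reading. But the word justifies using one rule in place of another in a power calculation, where the natural meaning is that the planned rule would do at least as well. In either sense, the article gives no power for the rule it will apply.

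Finally, BY is a valid, pre-specified choice with a stated reason. That too stands: its use is not an error.

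**Conclusion.** The point holds in conditional form. The quoted power belongs to a different rule from the planned one and is not a lower bound for it. BY power falls below Bonferroni power if fewer than roughly 14 CpGs or 4 markers respond, and equals or exceeds it otherwise. The direction is undetermined because no number of signals is stated. In the least favourable case, a single responder, the loss against Bonferroni is about 2 to 12 points with Δ as the between-arm difference and about 11 to 18 points with the control change subtracted. At ρ = 0.3 both single-signal figures drop below 80% even on the favourable reading.

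This assumes that the cited procedure is the arbitrary-dependence version with c(m), that the test is two-sided, and that all 200 women per group contribute both measurements. The conflict over the 0.1 SD control change is a separate matter and moves the power more than the choice of rule does on most of these settings. It is shown here only because the size of this point depends on it.

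Severity is moderate. Error control and the pre-specified tests are intact, and no change of sample size follows from this point alone.

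**What to change.** In the power section, remove *conservative* as an assurance and restate power under BY for a stated number of true CpGs and true markers. Include the single-signal case at 0.05/(m × c(m)), and say whether Δ is the intervention-arm change or the between-arm difference. The cost is a short recalculation and one or two sentences. The single-signal case needs no simulation, which also meets the computational reason given for using Bonferroni.

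Changing the procedure is optional and involves a trade. Benjamini-Hochberg gives more power than BY, but its guarantee relies on positive-type dependence, whereas BY's holds under any dependence. For the 12 markers, Holm controls the familywise error under any dependence and is never weaker than the Bonferroni rule used for power. It gains on BY when few markers respond and loses to it when many do. If BY is kept, the restated power is sufficient.

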### Randomization

All participants will provide written informed consent. Randomization will occur shortly after the baseline visit by study personnel. We will use block randomization (1:1 allocation) by self-reported body mass index (kg/m^2^) [18.5–24.9, 30+) and self-reported race/ethnicity (White non-Hispanic, White Hispanic, Black, Non-Hispanic or Black Hispanic, Other). The allocation sequence will be created by the biostatistician using computer-generated random numbers, and implementation will be through REDCap.

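### The simulated powers for CpGs and inflammatory markers do not follow from the printed scenario: about 88% (57%) and 74% (54%), against the stated 99% (82%) and 94% (84%)

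*Protocol article*

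**What the plan says.** The section Power and sample size calculations in the Protocol article gives every input. Measurements are simulated "according to a multivariate normal distribution with unit variance, assuming a within-subject correlation ρ". The control arm has a mean difference "comparing baseline to the 20-week (T2) visit equal to 0.1 SD units". The intervention arm has "a mean difference in the intervention group between the 20-week (T2) and baseline (T0) of Δ SD units". So Δ is a change within one arm, not a contrast between arms.

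The CpG threshold is 0.05/300000. The marker simulation reuses the same set-up, with a Bonferroni correction across 12 markers. With ρ = 0.5 (0.3), the results given are:

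- CpGs: "99% (82%) power to detect a mean difference in the intervention arm between baseline and T2 of Δ = 0.75 SD units"
- Markers: "94% (84%) power to detect a mean difference in the intervention arm between baseline and T2 of Δ = 0.45 SD units"

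Each figure is an average over 100 simulated datasets. The section on changes in inflammatory markers and methylation profiles sets the primary test as one of β3, "testing the interaction of randomization group with time, using a likelihood ratio test", using the baseline and 20-week visits.

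**The concern.** With two visits, β3 is the difference between the arms in mean change. If both arms move, the effect tested is the intervention change minus the control change, so a scenario with Δ = 0.75 and a control change of 0.1 offers a contrast of 0.65 SD. The stated powers look too high for that contrast.

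DNA methylation and inflammatory markers are primary outcomes, and this paragraph is the article's only account of their power. As printed, it tells the reader that power is at least 82% throughout. If the printed scenario is the intended one, a null marker result would later be judged against a power the design does not have.

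**Working it through.** **Inputs.** From Power and sample size calculations: 200 per group, unit variance, ρ = 0.5 or 0.3, control change 0.1 SD, Δ = 0.75 (CpGs) or 0.45 (markers), alpha 0.05/300000 or 0.05/12. From Randomization: 1:1 allocation. From the analysis section: a two-sided likelihood ratio test of β3 at two visits.

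**Formulas.** Variance of a subject's change = 2(1 − ρ). Standard error of the difference in mean change = √(2 × 2(1 − ρ)/200), which is 0.100 for ρ = 0.5 and 0.1183 for ρ = 0.3. Two-sided critical z is 5.233 for 0.05/300000 and 2.865 for 0.05/12. Power ≈ Φ(contrast/SE − z).

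**Step 1: what reproduces the stated figures.** Take the between-arm contrast as the full Δ, as if the control arm did not change.

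- CpG, ρ = 0.5: Φ(7.50 − 5.233) = 98.8%; stated 99%.
- CpG, ρ = 0.3: Φ(6.339 − 5.233) = 86.6%; stated 82%.
- Markers, ρ = 0.5: Φ(4.50 − 2.865) = 94.9%; stated 94%.
- Markers, ρ = 0.3: Φ(3.803 − 2.865) = 82.6%; stated 84%.

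The likelihood ratio version (Step 3) gives 98.5% (84.5%) and 94.8% (82.4%). All four stated figures agree with these within the error of 100 datasets, whose standard error is about 1 to 4 percentage points.

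**Step 2: the printed scenario.** The contrast is Δ − 0.1.

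- CpG, ρ = 0.5: Φ(0.65/0.100 − 5.233) = Φ(1.267) = 89.7%.
- CpG, ρ = 0.3: Φ(0.65/0.1183 − 5.233) = Φ(0.260) = 60.3%.
- Markers, ρ = 0.5: Φ(0.35/0.100 − 2.865) = Φ(0.635) = 73.7%.
- Markers, ρ = 0.3: Φ(0.35/0.1183 − 2.865) = Φ(0.093) = 53.7%.

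**Step 3: the test as planned.** The normal approximation is slightly generous so far into the tail. With two complete visits, the likelihood ratio statistic is 400 × ln(1 + t²/398), where t is the two-sample t statistic on change scores. It was simulated with 200,000 replicates.

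| Analysis | ρ | Stated | Normal approximation | Likelihood ratio | Chance that 100 datasets give at least the stated power |
|---|---|---|---|---|---|
| CpG, Δ = 0.75 | 0.5 | 99% | 89.7% | 88.0% | 4 × 10⁻⁵ |
| CpG, Δ = 0.75 | 0.3 | 82% | 60.3% | 57.3% | 1 × 10⁻⁷ |
| Markers, Δ = 0.45 | 0.5 | 94% | 73.7% | 73.5% | 1 × 10⁻⁷ |
| Markers, Δ = 0.45 | 0.3 | 84% | 53.7% | 53.5% | 1 × 10⁻¹⁰ |

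The last column is a binomial tail probability that uses the likelihood ratio power.

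**Step 4: other readings** (normal approximation).

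- Control change in the opposite direction (contrasts 0.85 and 0.55): 99.9% (97.4%) and 99.6% (96.3%). No match as a set.
- One-sided test, control change kept: 91.9% (65.2%) and 80.6% (62.5%). No match.
- Adjustment for baseline, variance 1 − ρ², control change kept: 98.8% (94.3%) and 88.0% (78.9%). No match as a set.
- Markers only, control change kept, alpha 0.05 without correction: Φ(3.50 − 1.960) = 93.8% and Φ(2.958 − 1.960) = 84.1%. This matches the stated 94% (84%), but contradicts the stated Bonferroni correction. The same omission does not explain the CpG figures, where it would give about 100% at both correlations.

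**The case against.** Four points can be made for the plan.

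First, the direction of the control change is not beyond doubt. The two arms' differences are worded in opposite order: baseline to 20 weeks for the control arm, 20 weeks and baseline for the intervention arm. If the signs differ, power is understated rather than overstated. This stands as an ambiguity, but the stated figures fail on that reading too. Movement in the same direction is the more natural reading.

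Second, a reader might infer that the authors simply forgot the control change, and that relabelling Δ as a between-arm difference would settle the matter. The document does not support that for the markers, because an omitted Bonferroni correction fits their two figures equally well. Relabelling could then dress an uncorrected result as a corrected one.

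Third, a reader might infer that the trial is too small. That does not follow. The article reports power at a given 200 per group and does not derive that number from a power target. If a between-arm difference of the full Δ is what was meant and simulated, the stated powers are about right for it. The error touches no estimand, test, alpha or conduct rule.

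Fourth, the use of only 100 datasets is disclosed, and its error of about 1 to 4 points is much smaller than the gaps found. It is a secondary matter and not the cause.

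**Conclusion.** The concern holds as an inconsistency between printed inputs and printed results. For the scenario as naturally read, power is about 88% (57%) for CpGs and about 74% (54%) for markers. The stated figures are higher by roughly 11 (25) and 20 (30) percentage points. Three of the four recomputed values fall below 80%.

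This rests on complete data at both visits for 200 per group, a control change in the same direction as the intervention change, the Bonferroni thresholds that the power section states, and one test per simulated dataset. Non-reproduction itself does not depend on the direction assumed. The claim that power is lower than stated does. Whether the control change was left out, or for the markers the correction was left out, cannot be decided from the document.

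**What to change.** 1. Check the simulation code for two things, separately for CpGs and markers: the control change (size and sign) and the alpha applied.
2. Rerun the printed scenario with the closed form or more replicates, and restate power as about 88% (57%) for CpGs at Δ = 0.75 and about 74% (54%) for markers at Δ = 0.45.
3. Word both arms' changes in the same order, so that their directions are clear.
4. Redefine Δ as the between-arm difference in change only where the code shows that this was simulated at the Bonferroni threshold. With a 0.1 SD control change in the same direction, the intervention-arm changes would then be 0.75 + 0.1 = 0.85 SD for CpGs and 0.45 + 0.1 = 0.55 SD for markers, and the article should say so.

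The cost is a code check, a short rerun and a corrected paragraph. Either the stated power becomes less favourable or the effect it refers to becomes larger. This correction changes neither the planned test nor the planned multiplicity procedure.

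### The detectable differences printed for weight, waist and fruit/vegetable intake (0.24 kg, 0.75 cm, 0.15 servings) are about eight times too small for the 98% power stated beside them

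*Protocol article*

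**What the plan says.** All of this is in the Protocol article, section Power and sample size calculations. For body weight, waist circumference and fruit/vegetable intake, the power figures "were based on a generalized linear model, using the R package pwr". The result given is: "A sample size of 400 subjects results in 98% power to detect an effect size of 0.05 or larger". This is for a two-sided alpha of 0.05. The same power is claimed for 20 weeks and for 1 year. The text does not say whether 0.05 is a standardised mean difference, an f², an R² or something else.

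The section then turns 0.05 into clinical units. With an SD of about 4.8 kg for weight, an "effect size of 0.05 or larger would correspond to a difference in weight change of 0.24 kg". With an SD of about 15 cm for waist, the result is a "difference in waist circumference change of 0.75 cm between the two randomized groups". With an SD of about 3 servings for intake, it is a "difference in fruit/vegetable consumption change of 0.15 servings between the two randomized groups". Each of the three is presented as detectable with 98% power.

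**The concern.** The three printed differences are exactly 0.05 times the quoted SD, so the text treats 0.05 as a standardised mean difference. A difference that small is far below what 400 women can detect with high power. Linear-model power routines commonly express effect size as explained variance, and on that scale 0.05 is a moderate effect. The conversion therefore appears to mix two scales.

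Weight, waist and intake are named primary outcomes in the abstract. These sentences are the article's only statement, in clinical units, of what the trial can detect on them. As printed, they overstate the trial's sensitivity several-fold.

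**Working it through.** **Inputs** (all from Power and sample size calculations): N = 400 in total; 1:1 allocation, that is "a sample size of 200 per group" in the biomarker calculation of the same section; two-sided alpha 0.05; stated power 98%; effect size 0.05; SDs 4.8 kg, 15 cm and 3 servings.

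**1. The printed differences.**
- 0.05 × 4.8 = 0.24 kg
- 0.05 × 15 = 0.75 cm
- 0.05 × 3 = 0.15 servings

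All three reproduce exactly, with 0.05 read as a difference in SD units.

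**2. The stated 98%.** I tried the standard readings of 0.05 with N = 400.

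| Reading of 0.05 | Power |
|---|---|
| Standardised difference d, two-sided, 200 per arm | 7.9% (noncentral t) |
| Standardised difference d, one-sided | 12.6% |
| f (so f² = 0.0025) | 16.9% |
| Correlation r | 16.8% |
| f², 1 / 2 / 3 tested terms | 99.4% / 98.5% / 97.4% |
| R² (f² = 0.05/0.95 = 0.0526), 1 / 2 / 3 tested terms | 99.6% / 98.8% / 98.0% |

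The f² rows use the noncentral F distribution with u and 399 − u degrees of freedom and noncentrality f² × N = 0.05 × 400 = 20. The R² row uses 0.0526 × 400 = 21.05. Only the explained-variance readings come near 98%.

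**3. What the printed differences would need.** For d = 0.05 and 98% power, n per arm = 2 × [(1.960 + 2.054)/0.05]² = 12,888, against 200 planned.

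**4. What 200 per arm detects with 98% power.** d = (1.960 + 2.054) × √(2/200) = 4.014 × 0.1 = 0.401 SD.
- Weight: 0.401 × 4.8 = 1.93 kg
- Waist: 0.401 × 15 = 6.02 cm
- Intake: 0.401 × 3 = 1.20 servings

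The ratio to the printed values is 0.401/0.05 = 8.0. For comparison, 80% power is reached at 0.28 SD (1.34 kg, 4.2 cm, 0.84 servings).

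**5. What f² = 0.05 means if it belongs to the group term alone.** With two equal arms f² = d²/4, so d = 2√0.05 = 0.447 SD: 2.15 kg, 6.71 cm and 1.34 servings, 8.9 times the printed values. The power at that difference is the one-term figure of 99.4%, not 98%.

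**6. Adequacy for the prior effects cited.**
- Weight: 3.9/4.8 = 0.81 SD, power essentially 100%
- Waist: 7.4/15 = 0.49 SD, power about 99.8%

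**The case against.** *The article never names f², so the cause is inferred.* This is correct. A reader might conclude that the authors used f² and misread it, but the text supports only something weaker: the metric is unnamed, and only an explained-variance measure gives about 98%. f² is the most likely candidate, and R² = 0.05 with three terms also gives 98.0%. The contradiction does not depend on which it was, since power for 0.24 kg with SD 4.8 and 200 per arm is about 8% in any case.

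*The planned regression adjusts for baseline, which reduces the residual SD.* It cannot close this gap. The residual SD would have to fall to 0.05/0.401 = 12% of the quoted value, which requires a correlation of √(1 − 0.1246²) ≈ 0.99. The quoted weight and waist SDs are moreover already attached to change from baseline.

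*The sample size is adequate anyway.* For the cited between-arm effects on weight and waist this stands (step 6). A reader might infer from the 8% that the trial is underpowered, but the documents do not support that. The 98% is attainable; what is wrong is its translation into kg, cm and servings.

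*A null result would be taken to exclude 0.24 kg.* A reader might expect this, but nothing in the article plans it. The analysis sections describe a likelihood ratio test of group, with no equivalence or futility claim.

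**Conclusion.** The point holds. The 98% power and the differences of 0.24 kg, 0.75 cm and 0.15 servings cannot both be true with 400 women. The printed differences have about 8% power. The differences that go with 98% power are about 1.9 kg, 6.0 cm and 1.2 servings, a factor of about eight. A factor of about nine is tempting, because f² = 0.05 converts to 0.447 SD, but for a single group term that difference carries about 99% power. If f² covers two or more terms jointly, the conversion to a group difference does not apply.

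These figures assume 200 analysed per arm with no losses, the quoted SDs, two-sided alpha 0.05 and no further gain from covariates. The error lies in the reported sensitivity for three primary outcomes, not in the adequacy of the design. For waist, however, the apparent tenfold margin (7.4 against 0.75 cm) shrinks to a narrow one (7.4 against 6.0 to 6.7 cm). The 7.3 servings cited for intake is an increase within the intervention arm, so it cannot be set against a between-arm detectable difference. The article gives no between-arm effect for intake.

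**What to change.** In Power and sample size calculations:

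1. Name the effect-size metric behind 0.05 and the number of terms tested.
2. Delete the 0.24 kg, 0.75 cm and 0.15 serving figures.
3. State instead that 200 per arm, with no losses, gives 98% power for about 0.40 SD, that is about 1.9 kg, 6.0 cm and 1.2 servings.
4. If the authors prefer to keep f² = 0.05 for the group term alone, give about 2.1 kg, 6.7 cm and 1.3 servings and change the power to about 99%. The two sets must not be mixed.
5. When the corrected differences are compared with earlier results, use the 3.9 kg and 7.4 cm effects only, not the 7.3 servings.

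The cost is wording. The stated sensitivity becomes less favourable, and the sample size, outcomes and analysis models do not change.
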